## Protocol

### Study design

This is a population-based prospective community- and facility-based observational study with a number of nested studies including incident case-control and incident trend studies to evaluate the impact of PCV10. To conduct the impact assessment, we are considering four outcomes: 1) IPD; 2) chest radiograph-confirmed pneumonia, 3) lung ultrasound-confirmed pneumonia; and, 4) NP carriage.

### Study site and population

The PCV Impact Assessment in Bangladesh study is being conducted in the Projahnmo study group’s research site in the Sylhet district of rural Bangladesh. The Projahnmo study group is a research partnership of the Johns Hopkins University with the Government of Bangladesh’s Ministry of Health and Family Welfare (MOHFW) and several Bangladeshi non-governmental organizations (NGOs): the International Centre for Diarrhoeal Disease Research, Bangladesh (iccdr,b); Shimantik; and Child Health Research Foundation (CHRF). The field site was established in 2001 to contribute to the improvement of maternal, newborn and child health by conducting clinical-epidemiological studies, intervention trials and program evaluations. The study area covers three
*upazilas* (sub-districts) of Sylhet district of Bangladesh (Zakiganj, Kanaighat and Beanibazar) with an estimated population of 770,000 (data source: project census, 2011), yielding an annual birth cohort of approximately 19,725 (
Figure 1). All households and women of childbearing age in the study area have unique current and permanent identification numbers, which allow for individual tracking and longitudinal follow-up. The study is being conducted among children 0–59 months old in this active surveillance area.

**Figure 1. f1:**
[figure not shown]
Study area. Pneumococcal Conjugate Vaccine impact assessment in Bangladesh.

The substantial existing infrastructure includes a census; a Global Positioning System-based map and background characteristics of the entire population; community- and facility-based surveillance; mechanisms for community-based sampling and case identification; referral, specimen collection, transport; state-of-the-art laboratories; and a data center. We have established community-based surveillance, which involves home visits by trained community health workers (CHWs) in the entire area in about 90,000 <5 year old children. Working closely with the Bangladesh MOHFW, we have established facility-based surveillance within the MOHFW sub-district hospital outpatient clinics and inpatient pediatric wards in the study area for potential IPD case detection, specimen collection, and transport. Project physicians who are trained and standardized to the study research protocols staff these facilities.

### Objective 1: Establish pre-PCV IPD rate

Trained female CHWs who are residents of the community and have at least a 10th grade education have been assigned to a population of about 10,000 individuals. Each CHW visits all households (about 2,000 households on average) in her area once every two months to update the population data by recording all new pregnancies, births, deaths, marriages and movements. Background data on age, parity, literacy, prior obstetric history and socio-economic status of all enrolled women in our study area were collected as part of previous or ongoing studies and are available in our database
^16^,^20^. These data are collected for all newly identified pregnant women who did not provide them previously. Similarly, dates of birth of children born in previous or ongoing studies are available in our database and the data are prospectively collected for women and children <5 years of age who were not part of prior studies. In our efforts to provide a standard package of care to pregnant women and newborns in this research site, CHWs provide information to pregnant women about care during pregnancy, delivery and the postpartum period during regular visits every two months. Families are encouraged to notify CHWs about all births as soon as possible using the existing cell phone-based birth notification system, and are encouraged to seek care from study designated hospitals for any illnesses in newborns and children. All children are visited every two months until they are 60 months of age, and data on their vital status, illness history and care seeking are recorded. Mothers and family members are educated during home visits every two months on signs of pneumococcal diseases (pneumonia, meningitis, and other IPD) and are further encouraged to visit the designated study hospitals for clinical evaluation, enrollment and management of suspected illnesses of the children.

The CHWs also recruit and supervise local resident village health workers (VHWs) in each village in the study area. The VHWs are provided with thermometers marked at a cutoff level of 101°F and trained on their use. They are also trained to recognize symptoms of pneumonia and meningitis. In addition, they visit and screen children of consented parents weekly for fever, respiratory problems and danger signs, and refer sick children to one of the study hospitals. The VHWs receive a monthly stipend and financial incentive payments for successful referrals of eligible children with clinical pneumonia, high fever, and meningitis. VHWs do not collect any study data but facilitate case detection and referral from surveillance population to the study hospitals. In case of refusal of referral advice by families, the VHWs call the CHWs for further facilitation of the referral process. The CHW referral criteria is in
Table 1.

**Table 1. T1:** Referral criteria for pneumonia and invasive pneumococcal diseases at the community level.

High fever (≥101.0°F)
Hypothermia (<95.9°F)
Movement only on stimulation
No movement/unconscious
Reported/Observed convulsions
Unable to feed
Vomits everything
Bulging fontanelle
Stiff neck
Lower chest indrawing
Observed head nodding/use of neck muscles in breathing
Noisy breathing
Cough/difficulty in breathing PLUS Fast breathing
H/O Scanty micturition or high colored urine PLUS Puffy face/Ascites/leg edema

In addition to family education for illness recognition and care seeking from sub-district hospitals, we have developed a network with the first-level facilities and private health care providers in both the formal and informal sectors within the study area and encourage them to refer sick children with suspected pneumococcal disease to the designated study hospitals. We have also included Sylhet Medical College and selected private tertiary level referral hospitals in Sylhet City in this network, which are frequent referral sites for children with symptoms of meningitis in our study area. We have mapped the first-level clinics and private health care providers in the study area including MOHFW’s Family Welfare Centers (FWCs), Community Clinics, NGO-supported clinics, village doctors and drug sellers. All of these providers are given an orientation on the study and are requested to refer eligible cases to the designated hospitals. The orientation includes standardized definitions of suspected pneumonia and meningitis cases and instruction on keeping a list of cases by village. Our study physicians periodically visit these providers and facilities to assess the quality of diagnoses made and reinforce adherence to the case definitions and protocols for referral of all suspected cases to designated health facilities. We identify community providers who see a particularly high volume of children <5 years of age with lower respiratory symptoms, and obtain the providers’ consent to station mobile teams of trained health workers at their offices. We have established a quality control program to ensure the quality of screening to maximize enrollment of eligible cases and of blood specimen collection to avoid specimen contamination. Periodic and need-based refresher trainings are organized for all study staff.

For referred cases of meningitis being treated in non-study hospitals, a trained study physician travels to visit the patient in that hospital, obtain parental informed consent, clinically screen the patient for suspected meningitis, and perform lumbar puncture if appropriate and if the parent provides consent. The cerebrospinal fluid (CSF) specimen is transported to the study laboratory using the procedures described below.

Upon presentation at any of the participating study hospitals, a research assistant requests parents/caregivers of all children <5 years of age to give consent for screening for suspected IPD (clinical pneumonia, meningitis, or high fever) and for collection of basic demographic and clinical information. Suspected IPD cases are identified by physicians at the study hospitals and mobile team members in the community. After obtaining written informed consent from parents, detailed data on demographic characteristics, clinical assessment, and history of medication use are recorded in a case report form (CRF). The criteria used for blood or CSF collection are provided in
Table 2.

**Table 2. T2:** Criteria for blood or CSF collection for testing for invasive pneumococcal diseases.

**Inclusion criteria**	1. Any of following danger signs i. Hypothermia (<95.9°F) ii. Movement only on stimulation iii. No movement/unconscious iv. Reported/Observed convulsions v. Unable to feed vi. Vomits everything vii. Bulging fontanelle viii. Stiff neck
	2. High fever (≥101.0°F)
	3. Moderate fever (99.5–100.9) PLUS Any of the following signs of severe pneumonia i. Chest indrawing ii. Observed head nodding during breathing iii. Stridor (persists after bronchodilatation)
	4. Suspected Nephrotic syndrome or Glomerulonephritis i. History of scanty micturation or high colored urine AND Oedema (Puffy face/Leg oedema/Ascities)
**Exclusion criteria**	1. Previously enrolled in the preceding 7 days
	2. Had received antibiotics doses (confirmed by prescription OR bottle/strip) and the last dose within last 24 hours

A blood sample (~3 ml) is collected from each eligible child and half of it is directly inoculated into a BACTEC (Becton Dickinson Diagnostic Instrument Systems, Sparks, MD, USA) pediatric blood culture bottle and kept at room temperature until transportation to the Sylhet laboratory, where it is processed in a BACTEC machine. The culture bottles that show signs of bacterial growth are then subcultured. The other half of the blood specimen is transported to the Sylhet laboratory maintaining cold chain for molecular testing.

Lumbar puncture is performed for all consented hospitalized cases with signs of meningitis. Up to 2 ml of CSF is collected for immediate plating on chocolate, blood and MacConkey agar media and a portion of CSF is saved for cytology and measurement of biochemical parameters. The remaining CSF specimen is preserved for molecular testing. All specimens are transported to the study laboratory in Sylhet at least twice daily for identification and real-time assessment of biological parameters. Preliminarily identified isolates are transported to the CHRF lab at Dhaka Shishu Hospital in Dhaka for reconfirmation, serotyping, and drug susceptibility testing. All molecular testing is performed in the CHRF lab in Dhaka using real-time polymerase chain reaction (PCR) techniques. The study doctors record data on treatment given, status at discharge and laboratory findings in the CRF. An IPD case is identified using a pre-determined criteria that take in to account the clinical findings, culture and PCR results. All sick children receive treatment based on the physicians’ clinical diagnosis. For outpatients, a written report on blood culture results is provided to parents at the next routine household visit after the results become available.

### Objective 2: IPD case-control and incident trend studies

We have maintained the IPD surveillance established for Objective 1 in our study area, including community surveillance, health facility activities and laboratory procedures, in order to detect IPD cases. The inclusion criteria for the case-control and incident trend studies are shown in
Table 3 and
Table 4. The age eligibility for enrollment in the IPD case-control study is shown in
Table 5 and the sample size requirement for IPD case-conrol study is shown in
Table 6.

**Table 3. T3:** Inclusion criteria for the IPD case-control study.

**Inclusion criteria**	1. Age 3–59 months meeting age-eligibility criteria under which they have had the potential to have started the PCV vaccine (not born yet or under age 12 months on March 25, 2015).
	2. Resident of the active surveillance area clinically eligible. a. For cases – clinically suspected invasive pneumococcal disease (pneumonia or meningitis or high fever) and pneumococcus isolated form blood or cerebrospinal fluid b. For controls-without any signs/symptoms of invasive pneumococcal disease as screened by physicians (hospital controls) or data collectors in the community (community controls)
	3. Written informed consent by parents/care givers.
**Exclusion criteria**	1. Refusal to join the study

**Table 4. T4:** Inclusion criteria for the incident-trend study.

**Inclusion criteria**	1. Age 3–59 months meeting age-eligibility criteria under which they have had the potential to have started the PCV vaccine (not born yet or under age 12 months on March 25, 2015).
	2. Resident of the active surveillance area
	3. Diagnosed clinically as invasive pneumococcal disease and pneumococcus isolated from blood or cerebrospinal fluid
	4. Written informed consent for participation in x-ray study by parents/care givers.
**Exclusion criteria**	1. Refusal to join the study

**Table 5. T5:** Age-eligibility criteria for inclusion in invasive pneumococcal diseases case-control study by study months. Age in completed months.

Year	2015					2016											
Month	Aug	Sep	Oct	Nov	Dec	Jan	Feb	Mar	Apr	May	Jun	Jul	Aug	Sep	Oct	Nov	Dec
Month of case- control study	1	2	3	4	5	6	7	8	9	10	11	12	13	14	15	16	17
Minimum age of eligibility	3	3	3	3	3	3	3	3	3	3	3	3	3	3	3	3	3
Maximum age of eligibility	15	16	17	18	19	20	21	22	23	24	25	26	27	28	29	30	31
Year	2017																
Month	Jan	Feb	Mar	Apr	May	Jun	Jul	Aug	Sep	Oct*	Nov*	Dec*	**If needed for adequate sample* *size*				

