### Aims and objectives

The primary aim of this study is to conduct a comprehensive evaluation of the national introduction of the PCV10 in Bangladesh measuring multiple outcomes. To accomplish this aim, we have established the following objectives for the study:

**Objective 1:** To collect data on community-based pre-PCV incidence rates of IPD in children 0–59 months of age in Sylhet district of Bangladesh.

**Objective 2:** To evaluate the effectiveness of PCV10 introduction on Vaccine Type (VT) IPD in children 3–59 months of age using an incident case-control study design. Secondary aims include measuring the effects of PCV10 introduction on all IPD, regardless of serotype, in children 3–59 months of age using the case-control study design, and quantifying the emergence of Non Vaccine Type (NVT) IPD.

**Objective 3:** To evaluate the effectiveness of PCV10 introduction on chest radiograph-confirmed pneumonia in children 3–35 months of age using an incident case-control study design. An additional aim is to estimate the incidence trend of clinical and radiologically-confirmed pneumonia in 3–35 month-old children in the study area before and after introduction of the PCV10
** vaccine.

**Objective 4:** To determine the feasibility and utility of lung ultrasound for the diagnosis of pediatric pneumonia in a large sample of children in a resource-limited setting. We also sought to evaluate the effectiveness of PCV10 introduction on ultrasound-confirmed pneumonia in children 3–35 months of age using an incident case-control study design and to examine the incidence trend of ultrasound-confirmed pneumonia in 3–35 month-old children in the study area before and after introduction of the PCV10 vaccine.

**Objective 5:** To determine the direct and indirect effects of vaccination status on NP colonization on VT pneumococci among children with pneumonia.

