## Discussion

The GoB MOHFW introduced PCV10 on March 2015, making it the second South Asian country to add PCV to their national vaccine schedule. While developed countries have seen significant decreases in pneumococcal disease after the introduction of PCV vaccines, there are a number of challenges that should be considered when introducing a new vaccine in resource poor settings such as in Bangladesh
^33^,^37^. First, pneumococcus has over 90 different serotypes, and the currently licensed vaccines contain only either 10 or 13 of the different serotypes. Additionally, the serotype distribution of the pneumococci that cause disease varies by location, and some countries have observed serotype replacement
^38^,^40^. GAVI currently provides co-funding for the introduction of vaccines such as PCV. Countries such as Bangladesh will be required to bear the financial burden for the implementation of all the vaccines including PCV, which is very expensive. Because of these issues, the WHO recommends that all countries have an assessment of the introduction of PCV10 to determine its impact in each setting.

The Pneumococcal Conjugate Vaccine Impact Study, expected to be completed in mid-2018, is a prospective community- and facility-based observational cohort study with a variety of nested studies including case-control and pre-post studies to evaluate the impact of PCV10 in Bangladesh. We designed a comprehensive, multiple outcome impact assessment because each outcome has its own strengths and drawbacks. Classic impact assessments generally measure and compare rates of IPD in vaccinated and unvaccinated children. However, there are several limitations to such a design. For example, not all IPD is associated with bacteremia, and the majority of cases of pneumococcal pneumonia are blood culture negative
^41^. Therefore, estimating the impact of vaccine on IPD alone will underestimate the burden of pneumococcal disease and will underestimate the true value of the vaccine. Additionally, many children arrive at health facilities with recent or current antibiotic use, increasing the difficulty to isolate pneumococcus in the lab from their specimen
^42^. To account for the attenuated estimate expected when measuring IPD rates and to get a more complete assessment of the impact of PCV10 in our population, we have considered 3 additional outcomes: 1) chest radiograph-confirmed pneumonia; 2) lung ultrasound-confirmed pneumonia; and 3) NP carriage.

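### Table 4 limits the IPD incident-trend study to the vaccine-eligible birth cohort and to x-ray-study consenters, leaving little or no pre-PCV baseline and confounding crude trends with age

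*Protocol article*

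**What the plan says.** In the protocol article, under Objective 2 (IPD case-control and incident trend studies), Table 4 is captioned "Inclusion criteria for the incident-trend study". Its first criterion repeats the first criterion of the case-control study (Table 3): "Age 3–59 months meeting age-eligibility criteria under which they have had the potential to have started the PCV vaccine", with the bracketed rule "not born yet or under age 12 months on March 25, 2015". Its third criterion defines a case as "Diagnosed clinically as invasive pneumococcal disease and pneumococcus isolated from blood or cerebrospinal fluid", so this is the IPD trend study. Its fourth criterion is "Written informed consent for participation in x-ray study by parents/care givers".

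The Study design section presents the trend studies as a means of evaluating the impact of PCV10. The Discussion describes "nested studies including case-control and pre-post studies to evaluate the impact of PCV10". A secondary aim of Objective 2 is "quantifying the emergence of Non Vaccine Type (NVT) IPD". The Introduction says that surveillance began on January 1, 2014 to supply pre-PCV IPD rates.

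**The concern.** A case-control study of vaccine effectiveness needs every child to have had a chance of vaccination, so the birth-cohort rule belongs in Table 3. A trend study needs the same age range observed in each period, and the rule prevents that in three ways.

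- Almost all child-time before introduction fails the rule, so there is little baseline to compare with.
- After introduction the eligible children grow older month by month. If IPD incidence falls with age, the crude rate falls too, whatever the vaccine does.
- Children aged 12 months or more at introduction are left out. They were not offered the vaccine, so indirect effects would show most cleanly in them.

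The x-ray-consent item is a separate difficulty. The case is defined by a blood or CSF isolate, which requires no chest radiograph.

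**Working it through.** The protocol states no event count or power for the IPD trend study, so there is no figure of its own to reproduce. The check is an account of child-time.

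**Inputs from the protocol article**
- Births: 19,725 per year (Study site and population), or 1,643.75 per month. Assumed uniform, with no mortality.
- Surveillance start: January 1, 2014 (Introduction). To March 25, 2015 this is 448 days, or 14.72 months.
- Expected IPD: about 50 cases in children under 5 in the year before introduction (Introduction). Treated here as aged 3–59 months, which is an approximation.
- Eligible ages by study month: minimum 3; maximum 15 in month 1, rising by one each month (Table 5). Table 5 is titled for the case-control study, but its ages follow from the same cohort rule, with a constant one-month offset.

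**Input assumed**
- k, the ratio of the IPD rate at 3–11 months to the rate at 12–59 months. The protocol gives no age-specific rates; the range used is 1 to 10.

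**1. Pre-PCV child-time that meets the cohort rule.** At t months before March 25, 2015, an eligible child is at least 3 months old and younger than 12 − t months. The eligible span is 9 − t months, and it is zero before late June 2014.
- Eligible: ∫₀⁹ (9 − t) dt = 40.5 child-months per monthly birth.
- All residents aged 3–59 months: 57 × 14.72 = 839 child-months per monthly birth.
- Share: 40.5 / 839 = 4.8%.
- In child-years: 40.5 × 1,643.75 / 12 ≈ 5,550, against 839 × 1,643.75 / 12 ≈ 115,000.
- All the eligible time is at ages 3–11 months. At 12–59 months there is none.

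**2. Expected pre-PCV cases kept, 12 months before introduction.** Share kept = 40.5k / (9 × 12 × k + 48 × 12) = 40.5k / (108k + 576).

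| k | Share kept | Of about 50 cases |
|---|---|---|
| 1 | 5.9% | 3.0 |
| 2 | 10.2% | 5.1 |
| 3 | 13.5% | 6.8 |
| 5 | 18.1% | 9.1 |
| 10 | 24.5% | 12.2 |

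**3. X-ray consent.** The article dates the start of the radiograph study in three ways: two months after introduction (Objective 3), August 2015 (Table 8) and September 2015 (Objective 5). All are after introduction. Read literally, no pre-PCV case could have given this consent, so none is kept. Objective 3 images children who meet the clinical pneumonia criteria, whereas Table 3 counts suspected IPD as pneumonia, meningitis or high fever. After introduction, IPD without clinical pneumonia would therefore drop out as well.

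**4. Ageing of the cohort with no vaccine effect.** In study month m the completed ages are 3 to 14 + m: nine monthly bands at 3–11 months and m + 3 bands at 12 months or more.
- Months 1–12: 108 infant bands and 114 older bands, total 222; mean age 12.6 months.
- Months 13–24: 108 infant bands and 258 older bands, total 366; mean age 18.4 months.
- Null ratio = [(108k + 258) / 366] / [(108k + 114) / 222].

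| k | Null ratio, months 13–24 vs 1–12 |
|---|---|
| 1 | 1.00 |
| 2 | 0.87 |
| 3 | 0.81 |
| 5 | 0.74 |
| 10 | 0.68 |

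This contrast is written in the analysis plan for Objective 3, not for IPD. It is borrowed only to show the size of the ageing effect.

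**The case against.** **No before-after ratio for IPD is written out.** The aims attach a comparison before and after introduction to the pneumonia trends of Objectives 3 and 4. The Objective 2 analysis says only that surveillance data will quantify IPD incidence and characteristics, and the Discussion's mention of pre-post studies names no outcome. This stands: a reader might infer that the protocol commits to an IPD pre-post ratio, and the text does not go that far. Even so, the trend studies are there to evaluate impact, and a trend confined to the eligible cohort serves that purpose poorly.

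**Vaccine-eligible children suit the coverage model.** The coverage section relates union-month incidence to coverage by Poisson regression. That analysis can use differences between unions and does not depend on a pre-PCV baseline. This also stands. It remains open to confounding if coverage rises over the months in which the cohort ages. Adjustment terms may be in the full plan; within the post-introduction cohort they could deal with ageing, but they cannot supply a pre-PCV comparator at 12–59 months.

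**A reader might infer that pre-PCV cases are lost and that non-vaccine-type emergence cannot be quantified.** The document does not support that. Objective 1 estimates overall, vaccine-type and non-vaccine-type rates without the Table 4 limits, and the surveillance was maintained. The difficulty is that those rates describe all children aged 0–59 months, a different population from Table 4.

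**A reader might also infer an artificial fall from a change of laboratory definition.** Table 4 asks for an isolate, while the Objective 1 case criteria "take in to account the clinical findings, culture and PCR results". But those criteria are not reproduced, Objective 2 says that laboratory procedures were maintained, and no PCR yield is given. No mismatch between periods is shown and none can be sized.

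**Both clauses look like drafting carry-over.** That is likely, and it makes the correction easy, but Table 4 as printed still defines the study.

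**Conclusion.** The concern holds for the trend study as Table 4 defines it. About 95% of pre-PCV child-time at 3–59 months is excluded, assuming uniform births and no mortality. The loss of cases is less certain, because it depends on an age pattern that the protocol does not give: about 76% to 94% for k from 10 down to 1 in the year before introduction, and all of them if the consent item is applied literally. A single count at the flat-rate end would overstate what is known.

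The possible spurious decline rests on the same assumed k and on a borrowed contrast. It disappears if incidence does not vary with age. The empty pre-PCV strata at 12–59 months and the exclusion of children aged 12 months or more at introduction do not depend on k.

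**What to change.** In Table 4:
- delete the birth-cohort clause from criterion 1 and delete criterion 4 (x-ray-study consent);
- count all resident IPD cases aged 3–59 months from January 2014, under the same stated laboratory case definition in every period;
- report age-specific or age-standardised vaccine-type and non-vaccine-type rates, with vaccine-eligible and age-ineligible children shown separately.

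With all residents aged 3–59 months counted in each period and a stable age structure, the expected ratio with no vaccine effect is 1.00 for any k, and the pre-PCV base is about 115,000 child-years instead of about 5,550.

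The cost is a change of wording and some added tabulation. Surveillance already covers all children under 5 and has run since January 2014. The Study status section has the IPD trend fieldwork continuing through June 2018, so no new data collection is needed.
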